### Strategies to improve adherence

Participants will have the opportunity to obtain chauffeured transport to each session and assessment locations at no cost. A weekly session will be dedicated to clarifying doubts about the diet plan with a nutritionist, and it will also be possible to contact the nutritionist by telephone, in order to facilitate access and adherence to the dietary plan. A social media group will be created to facilitate routine communication and remind participants of scheduled tasks. Throughout the study, the research team will assess participant's motivation and limitations. It is noteworthy that all participants are aware of the opportunity to attend the only clinic in Portugal that allows exercising within a hypoxic environment, with multidisciplinary supervision and free of charge.

### Study outcomes

The main outcome will be hemoglobin A1c levels after 8 weeks of interventions. A set of secondary clinical outcomes will include complete blood count with hemoglobin and reticulocytes, fasting glucose, fasting insulin, HOMA-IR, total-, LDL- and HDL-cholesterol levels, triglycerides, C-reactive protein, serum HIF1-α levels, systolic and diastolic blood pressure, body composition, cardiorespiratory and pulmonary gas-exchange variables. These outcomes will be evaluated at baseline and at the end of the study (eighth week), in all groups.

### Biochemical analyses

Blood samples will be collected after fasting for 12 h, no strenuous exercise in the last 24 h, and alcohol consumption in the last 72 h. Glycemic profile, namely hemoglobin A1c (%), fasting insulin (Uui/mL) and fasting glucose, and cardiovascular risk factors, namely total-, LDL- and HDL-cholesterol, triglycerides and C-reactive protein levels will be measured and expressed in mg/dL. Also, Serum HIF-1α levels (pg/mL) will be measured using the HIF1A Human ELISA Kit (EHIF1A Thermo Fisher Scientific, Milan, Italy) according the manufacturer's protocols.

### Blood pressure

Systolic, diastolic, and mean blood pressure will be measured using an automated sphygmomanometer (Dinamap Pro; Florida, United States), in the left arm, in a sitting position and after 10 min of rest, on the same day of blood sample collection. The measurements will be in triplicate and the average will be used and expressed in mmHg.

### Body composition

A stadiometer with 0.1 cm intervals will be used to measure height, and a digital scale accurate to 0.1 kg, and a maximum capacity of 150 kg, will be used to evaluate weight (Seca, Hamburg, Germany). Waist circumference (WC) will be measured with an inelastic tape placed at the midpoint between the anterior-superior iliac crest and the last rib, as hip circumference (HC) will be measured at the widest portion of the buttocks, with the tape parallel to the floor (Norton, 2018). The ratio between WC and HC will be obtained and expressed in cm. Body mass index will be calculated by the ratio between weight and squared height and expressed in kg/m^2 ^(Norton, 2018). Lean mass, fat mass, android and gynoid fat depots, and bone mineral density will be assessed by dual-energy X-ray absorptiometry (DEXA; GE® Lunar densitometer, DPX NTVR, with ENCORE 2011 software, version 13.60, GE Healthcare). Participants will be instructed not to perform other procedures with contrast or radiation the day before the measurement. The procedure will be performed after 12 h of fasting, in the supine position, with bare feet, light clothes and no metallic objects.

### Cardiopulmonary exercise test

All participants will complete a standard Bruce treadmill exercise test protocol (Myers et al., 2002) before and 48 h after the last exercise session, using an electrocardiogram and a face mask device to evaluate gas exchange (Cortex Metalyzer 3B®, Leipzig, Germany). The initial stage of the exercise involves walking on the treadmill at a speed of 2.7 km/h with a 10% gradient. After 3 min, treadmill speed and gradient are increased, with further increments every 3 min until the end of the test. Criteria for termination will be volitional fatigue or when 85% of age-predicted maximal heart rate ((220 – age)/0.85) is attained, or if any medical indications arise, or upon participant request. Exercise tolerance, cardiac and ventilatory responses will be obtained and a report with clinical conclusions will be made.

CPET uses non-invasive exercise stress testing to generate multiple variables that are then extrapolated from this data, including anaerobic threshold and VO_2_max, markers of aerobic capacity. Anaerobic threshold will be defined as the point at which minute ventilation increases disproportionately relative to VO_2_, a response that is generally seen at 60%–70% of VO_2_max (Albouaini et al., 2007). In our study, peak oxygen consumption (VO_2_peak), minute ventilation (VE), respiratory exchange ratio, and metabolic equivalent value will be measured. Capillary blood samples (25 µL) for blood lactate will be collected from the fingertip before and immediately at the end of the test (Lactate Pro, Arkay, Inc., Kyoto, Japan), such as heart rate, blood pressure and oxygen saturation. Borg rating of perceived exertion (6–20 points) will be recorded at the end of CPET.

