### Interventions

Volunteers who meet the inclusion criteria will be asked to sign a written informed consent before enrolment in the trial, with the principal researcher. Participants will be randomized into control (CTRL), EH or interventions (EH + LCD) groups during 8 weeks. The CTRL group will perform an exercise protocol in normoxia with a control diet, and the other groups will perform the same exercise protocol in hypoxia (simulated altitude – nitrogen dilution method), following a control diet (EH) or an LCD (intervention group). Thus, we will compare whether EH group is more efficient than exercise in normoxia (CTRL group) and, if by including a LCD (EH + LCD group) the effects of EH group would be potentiated. We emphasize that during all test, physical exercise professionals, nutritionist, and doctors or nurses will be available.

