### Statistical considerations

For sample and power calculations, this study is powered based on changes in hemoglobin A1c in RCTs included in the meta-analysis by Zuuren et al. (2018), which tested the effect of carbohydrate restriction up to 8 weeks. Considering a type I error of 5% and a power of 80% to detect differences at the dependent variable with a statistical significance when comparing 3 independent groups (CTRL versus EH and EH versus EH + LCD), and an effect size of 1.14, a sample size of 14 participants per group will be needed, totaling 42 individuals. With an assumption of a 20% dropout rate, we will recruit 48 participants. The sample size calculations were performed using the Statistical Power Analyses for Windows, (G*Power 3.1.9.4, Uni Kiel, Germany).

Statistical analysis will be performed using SPSS statistics software version 28.0, 2021 (IBM Company, Chicago, United States). All data will be reported as mean ± SD and statistical significance will be assumed at *p* ≤ 0.05. Pairwise comparisons will be analyzed using the Wilcoxon test. A two-way repeated measures ANOVA will be used to examine changes in cardiopulmonary parameters, body composition, glycemic profile, and cardiovascular risk factors over the chronic exercise period (0 vs. 8 weeks), and whether the magnitude of the chronic exercise-mediated adaptations differ between groups (EH vs. CTRL; LCD + EH vs. EH). When a significant main- or interaction-effect will be found, Bonferroni post hoc tests for multiple pairwise comparisons will be performed to identify differences between groups.

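### The exercise-test stopping formula gives 117.6% instead of 85% of predicted maximum heart rate, and a test ended at the intended 85% cap does not yield VO2peak

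*Protocol article*

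**What the plan says.** All of the test rules are in the Protocol article, section Cardiopulmonary exercise test. The stopping criteria are alternatives. The list opens with "Criteria for termination will be volitional fatigue" and continues with a heart-rate limit, to apply "when 85% of age-predicted maximal heart rate ((220 – age)/0.85) is attained". A medical indication or the participant's own request also ends the test.

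The next paragraph says what is taken from the test. It begins "In our study, peak oxygen consumption" and closes with "respiratory exchange ratio, and metabolic equivalent value will be measured". The same paragraph defines the anaerobic threshold. Lactate and heart rate are taken before and at the end of the test, and a Borg rating "will be recorded at the end of CPET".

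Study outcomes lists "cardiorespiratory and pulmonary gas-exchange variables" among the secondary outcomes. Under Statistical considerations, "A two-way repeated measures ANOVA will be used to examine changes in cardiopulmonary parameters" from week 0 to week 8, with comparisons between groups.

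**The concern.** Two things in the same section do not fit together.

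First, the words and the formula of the heart-rate limit disagree. The words put the limit below the predicted maximum; the formula puts it above. A stopping threshold should have one value, and anyone who programs the test from the bracketed expression would get the wrong one.

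Second, once the formula is corrected, the limit conflicts with the outcome named after it. A participant who reaches the cap is stopped because a preset heart rate has been attained, whether or not the limit of effort is near. The oxygen uptake recorded is then the value at that heart rate. A participant who tires first gives a value set by his or her own limit. Both would be reported as VO2peak. At stake is what a change in this secondary outcome over 8 weeks means.

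**Working it through.** **Inputs.** The limit in words (85% of age-predicted maximum) and the printed formula, (220 − age)/0.85, come from the section Cardiopulmonary exercise test. The article gives no age range and no resting heart rates. Ages 40 to 70 and resting rates r of 60 to 80 bpm are assumptions, used for illustration only.

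**Step 1: does the formula give 85%?** Let M = 220 − age. The words give 0.85 × M. The formula gives M / 0.85 = 1.176 × M, which is 117.6% of M at every age.

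| Age | M | Words, 0.85M | Printed, M/0.85 | Printed minus M | M minus 0.85M |
|---|---|---|---|---|---|
| 40 | 180 | 153.0 | 211.8 | 31.8 | 27.0 |
| 50 | 170 | 144.5 | 200.0 | 30.0 | 25.5 |
| 60 | 160 | 136.0 | 188.2 | 28.2 | 24.0 |
| 70 | 150 | 127.5 | 176.5 | 26.5 | 22.5 |

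(All in bpm.) The stated 85% is not reproduced. The printed limit lies 26.5 to 31.8 bpm above the predicted maximum, so taken literally it would rarely stop a test. Multiplying in place of dividing gives the figure in the words.

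**Step 2: how far short of maximum is the intended cap?** From the last column, 22.5 to 27 bpm below predicted maximum. As a share of the predicted heart rate reserve it is (0.85M − r)/(M − r). At age 60 and r = 70 this is (136 − 70)/(160 − 70) = 66/90 = 73.3%. Over the assumed ages and resting rates it runs from 67.9% (age 70, r = 80) to 77.5% (age 40, r = 60). A test ended there is submaximal by design.

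**Step 3: what does the change from 0 to 8 weeks then measure?** Consider the two ways of stopping at each visit:

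- Fatigue at both visits: a change in peak uptake.
- Cap at both visits: a change in uptake at a nearly identical preset heart rate. This is comparable within the person, but it is not a change in peak.
- Fatigue at one visit and cap at the other: a difference between two different quantities.

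The group mean change averages over whichever of these occur. The article does not give their frequencies, so the effect on VO2 cannot be sized.

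**The case against.** The strongest reply has four parts.

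*The slip has little practical effect.* The words state 85% plainly, the test has other stopping criteria and an electrocardiogram, and under Interventions "doctors or nurses will be available" throughout testing. This stands. A reader might infer from the table that participants will be driven to 188 bpm at age 60; the article does not support that.

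*VO2peak may simply mean the highest value reached, and the section calls variables extrapolated.* This stands only in part. On the first reading, the value in a capped test is still fixed by the stopping rule and not by the participant's capacity. The remark on extrapolation describes such tests in general and names anaerobic threshold and VO2max. For this study VO2peak is to be measured, and no method of extrapolating it is given.

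*Capped tests can be recognised.* This largely stands. End-of-test heart rate is recorded and age is collected (Data collection and management), so comparing the two identifies most capped tests. Respiratory exchange ratio, lactate and Borg rating help to show submaximal effort. None of these turns the value into a peak. That the article shows no data field for the reason a test ended is not an error in a condensed article.

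*VO2peak is not itself listed under Study outcomes.* That is correct. The outcome there is the wider set of cardiorespiratory and gas-exchange variables. Some members of that set, such as the anaerobic threshold, do not by definition need a maximal test, so the whole set is not undermined.

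**Conclusion.** Both parts hold, and the point is minor.

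The formula is wrong as printed: 117.6% against 85%, a gap of 188.2 − 136 = 52.2 bpm at age 60. The ratio needs no assumption; the bpm figures depend on the ages chosen.

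The outcome label is wrong for tests that end at the intended cap, and only for those. A reader might infer that VO2peak is invalid throughout the trial. That does not follow, because tests ended by fatigue can still yield it and the share reaching the cap is unknown. A reader might also infer a bias between the arms. The same rule applies to every arm at both visits, and nothing in the article shows that it acts differently by arm. The primary outcome, hemoglobin A1c, and the sample size do not depend on this test's stopping rule in any way shown.

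**What to change.** Print the limit as 0.85 × (220 − age). This costs nothing.

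If the cap stays:

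- Do not describe values from capped tests as VO2peak.
- Flag capped tests, either by end-of-test heart rate against 0.85 × (220 − age) or by a recorded reason for stopping.
- Base between-group conclusions on aerobic capacity on a submaximal measure that most tests can yield. One choice is VO2 at the anaerobic threshold, which the section already defines. Another is VO2 at a heart rate set low enough for nearly all participants to reach. A rate near the cap would not serve, since it is unobserved in anyone who tires earlier.
- Do not restrict the analysis to fatigue-ended tests. That would select participants on an event after randomisation.

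The cost is one corrected formula, one flag and one outcome definition. The downside is less comparability with studies that report true peak values.

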### Exercise protocol

Both exercises in normoxia and in normobaric hypoxia at 3.000 m of simulated altitude, will take place 3 times per week, during period intervention of 8 weeks, in a hypoxic chamber at CMEP – Exercise Medical Center, Porto – Portugal. The chamber allows to control O_2_ (11%–20.97%), temperature (until 50 °C), humidity (until 80%) and altitude (until 8000 m). Altitude rating can be defined as (a) high altitude: 1.500–3.500 m; (b) very-high altitude: 3.500–5.500 m and (c) extreme altitude: Above 5.500 m, over sea level (Mathew and Sharma, 2022).

Exercise sessions will consist of 45 min of moderate aerobic exercise on a cycle ergometer and treadmill (Life Fitness, Illinois, USA) and 15 min of strength training, as recommended for this population (Bull et al., 2020). Moderate exercise intensity, which is considered an efficient strategy to improve cardiorespiratory and metabolic health in T2DM (Gildea et al., 2021), will be defined using 75% of the heart rate reserve, quantified in the pre-intervention cardiopulmonary exercise test (CPET). During each exercise session, heart rate and oxygen saturation will be constantly monitored using a finger pulse oximeter (Globus YM201, Milan, Italy). All exercise sessions will take place at the same time of day (± 2 h) and visits will be separated by at least 48 h of recovery.

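### As worded, the exercise test can end at 85% of age-predicted maximal heart rate, yet its end value is reported as measured VO2peak; the printed formula contradicts that wording

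*Protocol article*

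**What the plan says.** All four statements are in the Protocol article.

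- **Stopping rule** (Cardiopulmonary exercise test): "Criteria for termination will be volitional fatigue or when 85% of age-predicted maximal heart rate ((220 – age)/0.85) is attained". A medical reason or the participant's own wish to stop also ends the test.
- **What is reported** (same section): "peak oxygen consumption (VO_2_peak), minute ventilation (VE), respiratory exchange ratio, and metabolic equivalent value will be measured". An earlier sentence there describes such testing in general as used to "generate multiple variables that are then extrapolated from this data, including anaerobic threshold and VO_2_max, markers of aerobic capacity". No extrapolation method and no criterion for maximal effort is given for this trial.
- **Outcome status** (Study outcomes): the secondary outcomes include "body composition, cardiorespiratory and pulmonary gas-exchange variables", assessed at baseline and week 8 in all groups.
- **Analysis** (Statistical considerations): "A two-way repeated measures ANOVA will be used to examine changes in cardiopulmonary parameters" between week 0 and week 8, and to compare those changes between arms (EH vs CTRL, EH + LCD vs EH).

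**The concern.** A test ended because a preset heart rate was reached has not shown the participant's peak oxygen uptake. It has shown uptake at that heart rate. A test ended by fatigue gives a symptom-limited value. The plan gives both the same name and analyses them as one variable. One person can also move from one kind of value to the other between visits, and that switch would be read as change.

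For anyone stopped by heart rate at both visits, end-of-test heart rate is the same number by construction. Ventilation, respiratory exchange ratio, lactate and perceived exertion at test end are then values at that rate, not at maximal effort. A lower resting heart rate alone can raise oxygen uptake at the fixed rate with no change in peak capacity.

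At stake is a statement about peak aerobic capacity that some of the tests did not observe.

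**Working it through.** **1. The stopping point, in words and as printed.** Predicted maximum = 220 – age.

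| Age | Predicted maximum | 0.85 × (220 – age) | (220 – age)/0.85 |
|---|---|---|---|
| 50 | 170 | 144.5 | 200.0 |
| 60 | 160 | 136.0 | 188.2 |
| 70 | 150 | 127.5 | 176.5 |

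The formula does not reproduce the worded 85%. Since 1/0.85 = 1.176, it lies at 117.6% of predicted maximum at every age, so a heart-rate stop would almost never act. The remaining steps apply only to the worded rule.

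**2. Could the worded limit act before fatigue?** The documents give no attainment rate. The Exercise protocol section sets training at 75% of heart rate reserve. Assume age 60 and resting rate 70. With the predicted maximum, the target is 70 + 0.75 × (160 – 70) = 137.5 bpm, against a test limit of 136. On that reading, participants train around the rate at which the test ends, so reaching the limit is plausible. If the reserve is instead taken from a test stopped at 136, the target is 70 + 0.75 × 66 = 119.5 bpm. Neither figure shows how many tests the limit would end.

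**3. Size for a participant stopped by heart rate.** The documents give no ages, resting rates or fitness levels, so these are assumptions. The fraction of heart rate reserve is taken to equal the fraction of VO2 reserve, resting VO2 is 3.5 mL/kg/min, and training does not change maximal heart rate.

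VO2 at end = 3.5 + (limit – resting HR)/(maximal HR – resting HR) × (true peak – 3.5)

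Age 60, resting rate 70, maximal rate 160, true peak 25:

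- Baseline: 3.5 + (66/90) × 21.5 = 19.27, which is 77% of 25.
- True gain 10% (to 27.5), resting rate unchanged: 3.5 + (66/90) × 24 = 21.10. The recorded gain is 1.83 against a true 2.5 (73%). In relative terms, 1.83/19.27 = 9.5%.
- Same gain, resting rate down 5 bpm: 3.5 + (71/95) × 24 = 21.44. The recorded gain is 2.17 (87% of true), or 11.3% relative.
- No true gain, resting rate down 5 bpm: 3.5 + (71/95) × 21.5 = 19.57, an apparent gain of 0.30.

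**4. Range.** Ages 50 to 70, resting rates 65 to 85, true peak 22, true gain 10% (2.2 mL/kg/min). The recorded baseline is 71% to 80% of true peak.

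| Fall in resting rate | Recorded / true absolute gain | Recorded relative gain (true 10%) |
|---|---|---|
| 0 to 5 bpm | 0.65 to 0.89 | 9.2% to 12.5% |
| 10 bpm | 0.96 to 1.09 | 12.0% to 15.3% |

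**5. Mixed stopping reasons.** Simulation with age 60 (SD 7), maximal rate 220 – age (SD 10), resting rate 72 (SD 8) and true peak 23 (SD 5). The share stopped by fatigue, taken to be at true peak, is set at 0%, 20% or 40%.

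- Mean recorded/true ratio: 0.78, 0.82, 0.87.
- True gain 2.30, no change in resting rate: recorded 1.69, 1.81, 1.93 (9.5%, 9.6%, 9.7%).
- True gain 2.30, resting rate down 5 bpm: recorded 2.00, 2.06, 2.12 (11.2%, 10.9%, 10.7%).

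The fatigue share is an input here, not a finding.

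**6. Is the anaerobic threshold a safe substitute?** The protocol places it at 60% to 70% of VO2max. With every test stopped by heart rate, about 15% of simulated tests end below 70% of true peak and 38% below 75%. Some recordings would hold little or nothing above the threshold.

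**The case against.** **The printed formula.** If it is what was meant, the heart-rate limit almost never acts and the values are essentially symptom-limited. This stands in full and makes the point conditional. The documents do not settle which of the two governs.

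**Extrapolation.** One might reply that maximal uptake is extrapolated. That sentence describes the test in general, whereas the statement about this trial says VO2peak is measured, and no method is given. This does not answer the point.

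**Most participants.** A reader might infer that most tests would be submaximal. The documents do not support that. Fatigue, medical indication and participant request are also stops, heart-rate-lowering drugs are not among the listed exclusions, and no attainment rate appears.

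**Understated training effect.** A reader might also infer that the trial will typically understate the benefit. That holds mostly for absolute change. Relative change is roughly preserved or somewhat overstated. Standardised change goes either way: with every test stopped by heart rate, the baseline SD shrinks from 4.98 to 4.09, so the gain is 1.69/4.09 = 0.41 SD with no heart-rate change or 2.00/4.09 = 0.49 with a 5 bpm fall, against 2.30/4.98 = 0.46 true.

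**Between-arm bias.** All arms exercise under the same test rule, and the figures above are within-person changes. A wrong between-arm conclusion is possible if heart-rate adaptation or stopping reasons differ by arm, but it has not been shown.

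**Conclusion.** The point holds as a conditional labelling and pooling fault in a secondary outcome. Under the worded 85% rule, each test stopped by heart rate yields oxygen uptake at a preset rate, about 71% to 80% of true peak in the modelled range. The plan pools it with symptom-limited values under the name VO2peak.

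How many participants this affects is unknown. The size and direction of the distortion depend on the scale used and on how heart rate changes with training. All magnitudes rest on the assumed linear relation and on assumed ages, resting rates and fitness.

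The worded rule (136 bpm at age 60) and the printed formula (about 188 bpm) contradict each other and must be reconciled. This review does not choose between them. HbA1c and its sample size are not directly affected.

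**What to change.** First, reconcile the worded limit with the printed formula. The stopping rule itself is for the clinical team.

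If the worded rule stands:

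1. Name the end value *VO2 at test end*, and record the reason for stopping at both visits.
2. Compare arms on submaximal measures from the existing recordings: VO2, ventilation, respiratory exchange ratio and heart rate at the last Bruce stage that the participant completed at both visits. Add VO2 at the anaerobic threshold where it can be identified, and report how many tests do not allow this. The threshold should not be the sole cardiorespiratory outcome.
3. Limit any VO2peak statement to participants who stopped from fatigue at both visits, and label it descriptive.

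The cost is wording in the outcome and statistics sections, one recorded field per test and a re-reading of the gas-exchange files. No extra test, visit or participant is needed. The trial gives up a general claim about VO2peak, and some thresholds will be unreadable.
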